**Methodology**: This study will be done in Masindi and Kiryandongo districts in western Uganda. We plan to conduct three sub studies: Sub study one, a descriptive cross-sectional study with healthcare workers and health managers; using structured questionnaires, Focus Group Discussions and Key Informant Interviews. Sub study two is a cross-sectional population based observational study targeting lactating women, traditional birth attendants and elderly caregivers; using Key Informant Interviews with TBAs and Elderly caregivers, In-Depth Interviews and Structured Interviews with lactating mothers. Sub study three a community intervention trial allocating health centres to two different arms (routine ANC care only; routine ANC care and CHWs offering standardized prenatal education at the primary care facility plus standardized mobile phone reminders through CHWs).

**Statistical analysis plan**: Qualitative data will be audio taped, transcribed verbatim, translated in to English and analysed for emerging themes. Quantitative data will be entered in to Epidata 2002 computer software package, cleaned and exported to stata version 10.0 for analysis. Data on knowledge and perception of health workers together with data on common maternal and newborn homecare practices will inform the design for sub study three. In sub study three we will measure timely return ANC visits, completed antenatal care visits, number of institutional deliveries and homecare practices in the two arms. Analysis will be done in stages: univariate to generate frequencies, bi-variate analysis will be done to establish associations between variables of interest. Chi-square tests will be used to establish significant associations; at the Multivariate level, analysis will be run to get Odds Ratio values, 95% CI for the OR and the respective p-values will be presented.

**Dissemination and utilisation**: Results of this study will be shared and discussed with district local authorities and the Ministry of health officials; presentations will be made in national and international conferences and; publications in peer reviewed journals. These findings will specifically inform the ongoing debate on antenatal care service improvement and contribute to the attainment of MDGs 4 and 5.

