### 4.4.8 Sample size

Using the formula for cluster randomised trials suggested by Hayes and Bennett ([Hayes and Bennett 1999](#_ENREF_36)),

**n = D(Z_α/2_ + Z_β_)^2^[π_0_(1- π_0_) + π_1_(1- π_1_)]/ (π_0 +_  π_1_)^2^** where

- **n** = number of participants in each arm,
- **D** = the design effect of 2.5,
- **Z_α/2_** = 1.96,
- **Z_β_ = 0.84,**
- **π_0_ =** current rate of institutional deliveries, 23.5%
- **π_1_** = estimated rate of institutional deliveries after the intervention, 33.5%

Substituting in the formula, we obtain a sample size of 788; allowing for a 10% loss-to-follow up we estimate a total population of 868 participants per arm. Further substituting in the formula for required number of cluster, C

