**C=1+(Z_α/2_ + Z_β_)^2^[π_0_(1- π_0_)/n + π_1_(1- π_1_)/n + k^2^(π_0_^2^ _+_ π_1_^2^)]/ (π_0 +_ π_1_)^2^**

Substituting for n=868, we arrive at a cluster number of 8 per arm; two arms will therefore require 1,736 participants distributed between 16 health centres; implying an average of 108 pregnant women enrolled per health centre for the entire four months. This will necessitate recruiting an average of 27 pregnant women per health centre per month.

This sample is based on the following assumptions:

- A degree of error, 0.05
- (95% confidence interval, **Z_a_** =1.96),
- the power to detect a significant difference between two comparison groups of 80% (**Z_a/2_** =0.84) to detect a 10% difference;
- **π_0_**, the current prevalence of institutional deliveries 23.5% ([DHO 2010](#_ENREF_28));
- **π_1_**, expected prevalence of institutional deliveries after the intervention 33.5% and
- A design effect **D,** 2.5 and
- Coefficient of variation between clusters of the same group **k_m_,** 0.25

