**4.4.10 Data management and analysis**

At the end of each trail day, data will be collected, sorted and checked for consistency and for completeness. Open-ended questions will be categorized. All data collected will be entered in Epi-data soft ware package and exported to stata 8.2 soft ware package for more analysis. This analysis will be done in stages: univariate analysis ,where frequencies of variables will be generated and tabulated to establish the extent of use of these ANC services in the standard health centre setting compared to the second arm where extra education, and telephone remainders will be made. This level will also show the factors influencing timely return ANC visits, completion of the four recommended ANC visits, institutional deliveries and newborn care practices (Provision of warmth to the newborn, Initiation of breastfeeding within one hour of birth, Care for the cord and Immunization for the newborn-Polio 0 & 1; BCG within the neonatal period). At bi-variate level of analysis, cross tabulations will be run to establish associations between variables of interest. Chi-square tests will be used to establish significant associations. At multi variate analysis, all variables that will be found to be statistically significant at bi-variate ,will be subjected to the multivariate model (logistic) to control for confounding. The analysis will be run to get Odds Ratio values, 95%CI for the OR, and the respective p-values will be presented. Finally the primary outcomes of interest will be compared between the two arms i.e. a standard arm and the new trial arm upon which conclusions will be drawn.

*Quality Control*

To control quality of data to be collected,(completeness, correctness and consistency), the following measures will be undertaken:

Research assistants will be selected and trained by the principal investigator, questionnaires will be pre-tested for one day in a few selected health centres in Masindi and Kiryandongo. Completed questionnaires will be collected and checked by the principal investigator. Data collection will be carried out under strict supervision of the principal investigator. Data editing will be done and corrections will be made there at the selected health centres.

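### The trial is sized on a 10-percentage-point difference, but the odds ratio is the only effect measure planned with a confidence interval, and no stated interval or test allows for health-centre clustering

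*Protocol*

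**What the plan says.** Protocol section 4.4.8 plans on two proportions: "current rate of institutional deliveries, 23.5" per cent and "estimated rate of institutional deliveries after the intervention, 33.5" per cent. Its list of assumptions gives the target as 80% power "to detect a 10% difference", and the calculation uses "the design effect of 2.5". It arrives at 788 women per arm, raised to 868 for 10% loss to follow-up.

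Section 4.4.10 describes the analysis in steps: frequencies for the standard setting against the second arm, cross-tabulations with chi-square tests, then a logistic model to control for confounding. The effect measure follows: "The analysis will be run to get Odds Ratio values, 95%CI for the OR, and the respective p-values will be presented". The abstract says the same under its statistical analysis plan: "analysis will be run to get Odds Ratio values, 95% CI for the OR and the respective p-values will be presented". Section 4.4.10 ends by saying that the primary outcomes will be compared between the arms and conclusions drawn, without naming a measure for that step.

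For sub-study three, neither place mentions a risk difference or risk ratio with an interval, or any allowance for health centres as clusters.

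**The concern.** The quantity that justified the sample size is the percentage-point gain in institutional delivery. As written, the trial would give no interval for that gain. A reader could subtract one tabulated percentage from the other, but the result would be unadjusted and without a statement of precision. Adjustment matters here because section 4.4.9 assigns health centres to arms purposively, not at random.

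The outcomes with a documented rate are also common. For common outcomes the odds ratio lies well away from the risk ratio, and equal absolute gains on different outcomes give different odds ratios. The abstract says results will go to district authorities and Ministry of Health officials, who need to know how many more women per hundred deliver in a facility or complete four visits.

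The missing clustering allowance affects any interval that is reported, on either scale. If the assumed design effect holds, intervals that ignore it will be too narrow.

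**Working it through.** **Inputs.** From 4.4.8: control rate p0 = 0.235, intervention rate p1 = 0.335, Z values 1.96 and 0.84, design effect D = 2.5, loss 10%. From 4.1: fourth antenatal visit 29.4%. From 4.3.5: good cord care 42%, the planning figure for sub-study two (cord care is also an outcome of sub-study three in 4.4.7).

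**1. Reproduce the plan's sample size.** p0(1 − p0) + p1(1 − p1) = 0.179775 + 0.222775 = 0.40255.

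n = 2.5 × (1.96 + 0.84)² × 0.40255 / (0.335 − 0.235)² = 2.5 × 7.84 × 0.40255 / 0.01 = 789.0. The stated figure is 788, and 789 × 1.10 = 868. The match needs the difference p1 − p0 in the denominator; with the plus sign as printed the formula gives about 24, so the sign looks like a typing slip. The planned effect therefore enters the sample size as a percentage-point difference.

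**2. The same effect on three scales.** OR = [p1/(1 − p1)] / [p0/(1 − p0)] and RR = p1/p0. For delivery, OR = (0.335/0.665)/(0.235/0.765) = 1.64 and RR = 0.335/0.235 = 1.43. The other rows assume the same 10-point gain.

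| Outcome | Rates | Difference | RR | OR |
|---|---|---|---|---|
| Institutional delivery | 23.5% to 33.5% | 10 points | 1.43 | 1.64 |
| Four antenatal visits | 29.4% to 39.4% | 10 points | 1.34 | 1.56 |
| Good cord care | 42% to 52% | 10 points | 1.24 | 1.50 |

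The odds ratio's excess over 1 is 1.5, 1.65 and 2.1 times that of the risk ratio in the three rows.

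**3. Intervals at the planned rates, with the design effect.** Effective n = 788/2.5 = 315 per arm; Wald intervals.
- Difference: SE = √(0.40255/315.2) = 0.0357; 10.0 points (95% CI 3.0 to 17.0); z = 0.10/0.0357 = 2.80.
- Odds ratio: SE of log OR = √[1/(315.2 × 0.179775) + 1/(315.2 × 0.222775)] = 0.1786; 1.64 (1.16 to 2.33); z = 2.77.
- Risk ratio: 1.43 (1.11 to 1.84).

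**4. The same intervals with clustering ignored.** Each standard error shrinks by √2.5 = 1.58.
- Difference: 10.0 ± 7.0/1.58, or 5.6 to 14.4 points.
- Odds ratio: SE of log OR = 0.1786/1.58 = 0.113, giving 1.31 to 2.05.

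**The case against.** The strongest reply is that a pair of proportions implies no single scale: 23.5% and 33.5% are equally a 10-point difference, a risk ratio of 1.43 or an odds ratio of 1.64. Planning on two proportions and analysing by logistic regression is ordinary practice and tests the same null hypothesis. The z values (2.80 and 2.77) bear this out. All of that stands, so there is no fault in power or sample size here.

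Three stronger readings are tempting, and the documents do not support them.
- A reader might infer that nothing but odds ratios will be reported. Section 4.4.10 also tabulates frequencies by arm and plans a comparison of the primary outcomes. What is absent is an interval for the difference.
- A reader might infer that the odds ratio will exaggerate the result. It does so only if it is taken for a relative risk, and the protocol nowhere says it will be described that way.
- A reader might infer that an adjusted odds ratio shuts off the percentage-point scale. The coefficient alone does not give the difference, but the fitted logistic model does, by averaging predicted risks under each arm.

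It is also fair to say that making a crude difference the headline would be a poor trade with purposive assignment. The difference should be adjusted and should stand beside the odds ratio, not replace it.

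Finally, an analysis plan that is not shown might add an absolute measure. But the protocol itself names the measure with its interval in two places, and neither place covers the planned effect or the clustering.

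**Conclusion.** The point holds as a defect of estimation and reporting. The protocol plans no confidence interval for the quantity it was sized to detect, and none of its stated tests or intervals allows for health-centre clustering. At the planned rates the reported result would be an odds ratio of 1.64, against a risk ratio of 1.43 and a difference of 10 points. If clustering is ignored and the design effect of 2.5 is right, intervals are too narrow by a factor of 1.58.

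The delivery figures use the protocol's own planned rates. The rows for four visits and cord care assume a 10-point gain that the protocol does not state for those outcomes, and the 42% is taken as the control rate for cord care. The protocol gives no rate for timely return visits, warmth, early breastfeeding or newborn immunisation, so nothing is claimed about how far the two ratios would diverge there.

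**What to change.** In 4.4.10, and in matching words in the abstract, state that each primary outcome will be reported as:
- the percentage in each arm;
- the confounder-adjusted difference in percentage points, for example by averaging predicted risks from the planned logistic model with every woman set to each arm in turn, with a 95% CI that allows for health-centre clustering;
- the odds ratio from the same model, with the same clustering allowance in its interval and p-value.

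State also that these estimates serve the closing comparison between arms, which now names no measure. With only 16 health centres, the clustering method should include a small-sample correction.

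The cost is a little more analysis work and intervals that are wider and less favourable than unclustered ones. No new data are needed, and the planned 868 per arm does not change on account of this addition.

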## 4.4.1 Introduction

The ultimate intervention will be based on data obtained from the two formative surveys and; based on our own knowledge about the context of Masindi and Kiryandongo and the subject of maternal and newborn care. The first study with health workers will inform the design of re-orienting health services at the antenatal clinic, while the community survey will form a basis for the appropriate educational messages to be delivered at the ANC clinics.

Primary outcomes of interest in this study are timely return ANC visits, completed four ANC visits, institutional delivery, and neonatal homecare practices. Secondary outcomes are post intervention community and health workers perceptions about the educational intervention offered by CHWs at the primary care facility.

The educational intervention will consist of **i)** a promotional team of community health workers supervised by a health assistant providing educational interventions at the primary care facility and; **ii)** the promotional team at the health centre using mobile phone reminders through Community Health Workers to pregnant women at the households.

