**A: Socio-demographic characteristics**

1. Code number..........................................................................................
2. Name of household Head........................................................................
3. Age of Respondent in completed years (lactating woman)....................
4. Parity of respondent 1, 2, 3, 4, 5, over 5
5. Highest education level attained:
6. Non
7. Primary;
8. Secondary;
9. High school;
10. Tertiary;
11. Marital status:
12. Married
13. Single
14. Separated
15. Divorced
16. Widowed
17. What do you do for a living:
18. Nothing
19. Housewife
20. Farming/gardening
21. Selling in the market/petty trade
22. Business woman
23. Salaried
24. Did you attend any ANC during the last pregnancy:
25. Yes, 2. No
26. Number of ANC visits made with the last pregnancy:
27. 0,
28. 1,
29. 2,
30. 3,
31. 4
32. More than 4
33. Where did this last delivery take place:

**1)** Home;

**2)** Health facility;

**3)** On the way to health Facility

1. How old is the baby now? Age in completed weeks
2. 0-1 week **2)** 2-4 weeks **3)** 5-8 weeks **4)** 9-13 weeks
3. Number of living children: 1, 2, 3, 4, 5, 6, more than 6
4. Number of deceased children: 0,1, 2, 3, 4, 5, 6, more than 6

(*if deceased babies is* ***0*** *then skip to section* ***B***)

1. At what ages did the deceased children die?

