# Annex 15: SOPs: Standard Operating Procedure and intervention packages

### i) Standard operating procedure and intervention package for educational intervention during ANC

**(**[**Bhutta Z, Sajid S et al. 2011**](#_ENREF_10)**)**

When the pregnant women enter the clinic room

1. Identify pregnant women with all of the following conditions:
2. First visit of the current pregnancy,
3. Not more than 28 weeks of gestation
4. Administer the consent form
5. If she consents then open a file for her
6. Request for her ANC card
7. Enter all personal details available on the ANC card in to the file
8. Record any telephone contacts that you can use to access her in future

name, age, ethnicity, parity, LNMP, EDD, gestation age of the first visit, history of previous pregnancy outcome of the previous pregnancy (baby – alive or dead, mode of delivery), distance from the health facility, marital status, history of previous ANC attendance-Number of attendance, delivery (home, health facility, TBA etc).

Note the date for the next appointment, (all this information will be used to tailor the discussions)

-if she consistently attended all the expected milestones-then you find out what her motivation was to do so, and whether she plans to do the same for the current pregnancy;

- If not consistent-discuss the reasons for inconsistencies and help her to find a solution,

- diet during pregnancy-find out what foods are readily consumed and what she can easily afford, what foods could be prohibited during pregnancy (caution about antagonising cultures-you can find another acceptable alternative source of the food value) and discuss the importance for balances in diet, fruits, green vegetables, proteins and carbohydrates,

- Discuss work related activities-how much she does and who helps her with the routine household and garden chores.

- Discuss importance of ANC even when she has been attending consistently, the advantages of delivering in the health facility even when she has been delivering at the health facility,

- Birth preparation-clean clothes for the newborn (emphasis that clean does not mean new!-even old rages can be patched together washed clean, clean environment for the newborn,

- caring for the cord, dangers of applying substances to the cord,

- Pre-lacteal feeds-and its disadvantages-explain how breast milk eventually comes and the usefulness of colostrum.

- Discuss bathing of the new baby how soon and how to delay (delay up to 24 hours),

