- Immunisation of the child, polio 0, BCG etc.

- Recognition of a sick child-hot to touch, refusing to feed, crying unusually,

All these information should be derived from discussions with the pregnant woman-not as a set of instructions to be strictly followed-compromises should be made at every stage-all that is agreed upon should be detailed down in the file. The counsellor should moderate the discussions, if the pregnant woman has come with a partner or a caretaker; both of them should be involved in the discussions even if the care taker is not pregnant-if there is a caretaker present then this should be recorded and state the relationship between them.

Tick the areas that were discussed, mark with a cross what you did not discuss with her, note down important decisions that you have agreed upon with the participant-you will use this as a reference point in subsequent meetings and discussions

Ensure that the discussion does not exceed 30 minutes unless there is expressed interest from the participant to continue. And this expression should be noted down in the file.

For subsequent visits indicate appointment dates and actual revisit dates

Later on follow-up for delivery and record where she has delivered from

Assess for the different practices outlined annex 6 will be used to assess the following outcomes

Place of delivery, Cutting of the cord, care for the cord, initiation of breast feeding, provision of pre-lacteal feeds, in case of illness how it was recognised, what action was taken, how soon was the care seeking from onset of disease or when the decision was made that the child was unwell, what facility did she take the child, outcome, at the periphery of assessment the researcher will want to know whether the child is still alive just at one month.

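### The arm comparison fixes no term for the pre-trial level of any outcome, although centres are purposively allocated by location, and the two baseline items that could supply one are documented only in the intervention procedure

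*Protocol*

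**What the plan says.** **Analysis.** Section 4.4.10 runs in stages: frequencies, cross-tabulations with chi-square tests, then a logistic model containing the variables that were significant at the bivariate stage, to control for confounding. It closes with: "Finally the primary outcomes of interest will be compared between the two arms i.e. a standard arm and the new trial arm". Conclusions are drawn from that comparison. Section 4.4.7 lists the two arms as the only independent factor.

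**Allocation.** Under section 4.4.9, eight centres are purposively assigned to each arm, and centres at the two extremes of the districts go to one arm or the other to avoid contamination. Section 5.1 repeats this.

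**Baseline items on the woman.** The ANC education procedure in Annex 15 (i) lists among the details to enter in her file: "history of previous ANC attendance-Number of attendance, delivery (home, health facility, TBA etc". Annex 15 (iii) has the health assistant ensure that CHWs enter and archive the details. Annex 9 shows the control arm with no CHW deployed.

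**Sub-study two.** Its form, Annex 6, asks "Where did this last delivery take place" and also covers number of ANC visits, cord care, warmth and immunisation. Annex 15 (i) reuses that form in the trial: "Assess for the different practices outlined annex 6 will be used to assess the following outcomes". Section 4.4.1 gives the survey one use in the trial: "while the community survey will form a basis for the appropriate educational messages to be delivered at the ANC clinics".

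**The concern.** Under random allocation, a difference between arms in pre-trial facility delivery would be chance, and the test would allow for it. Here allocation follows geography, with eight centres a side, so an existing difference between the two areas is indistinguishable from an effect of the package in a comparison of follow-up outcomes. It could create an apparent benefit or hide a real one.

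A significance screen does not deal with this. Whether previous place of delivery enters the model would depend on the data, and the screen never builds a centre-level baseline. It also cannot adjust the arm comparison for a variable that one arm lacks. On the text as it stands, control women may lack it: the items sit in the intervention procedure, and Annex 6 asks about the latest delivery and the birthplace of deceased children, but not about earlier surviving children. If this is not settled before enrolment, the information may be hard to recover.

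A second cost is precision. Part of the variation between centres is probably stable over time, and a baseline term could take some of it out of the error.

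**Working it through.** **Inputs (sections 4.4.8 to 4.4.9).** "current rate of institutional deliveries, 23.5"% (p0); "estimated rate of institutional deliveries after the intervention, 33.5"% (p1); "A degree of error, 0.05", taken as two-sided; between-cluster coefficient of variation k = 0.25; 8 centres per arm; 868 women per arm with 10% loss, so m = 868 × 0.9 / 8 ≈ 98 followed per centre. The correlation r between a centre's pre-trial and follow-up rates is not given. I assume 0.3, 0.5 and 0.7.

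**The plan's own figure.** n = 2.5 × (1.96 + 0.84)² × [0.235 × 0.765 + 0.335 × 0.665] / (0.335 − 0.235)² = 2.5 × 7.84 × 0.40255 / 0.01 = 789, against 788 stated. It reproduces with a minus sign in the denominator, where the formula is printed with a plus.

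**Precision without a baseline term.** Var(difference) = [k²(p0² + p1²) + (p0q0 + p1q1)/m] / 8, where q = 1 − p.
- Between centres: 0.0625 × (0.055225 + 0.112225) = 0.010466
- Within centres: 0.40255 / 98 = 0.004108
- SE = √(0.014573 / 8) = 0.0427, or 4.3 points
- Between-centre share = 0.010466 / 0.014573 = 72%
- Effect/SE = 0.10 / 0.0427 = 2.34; noncentral t on 14 df gives power of 59%

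**With a centre-level baseline term.** Only the between-centre part is multiplied by (1 − r²), and df falls to 13.

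| r (assumed) | SE | effect/SE | power |
|---|---|---|---|
| none | 0.0427 | 2.34 | 59% |
| 0.3 | 0.0413 | 2.42 | 61% |
| 0.5 | 0.0387 | 2.59 | 67% |
| 0.7 | 0.0344 | 2.91 | 77% |

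**Bias with no intervention effect.** SE = √([2 × 0.0625 × 0.055225 + 2 × 0.179775 / 98] / 8) = 0.0364. With a pre-existing gap d between the areas and a correct centre-level t-test on 14 df:

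| d (assumed) | d/SE | declared significant |
|---|---|---|
| 3 points | 0.83 | 12% |
| 5 points | 1.38 | 25% |
| 8 points | 2.20 | 54% |

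For scale, k = 0.25 implies a between-centre SD of 0.25 × 23.5 = 5.9 points. Even random allocation of eight against eight would then give true gaps with an SD of 5.9 × √(2/8) ≈ 2.9 points. The document gives no rates by area, so the actual gap is unknown.

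**The case against.** The best reply is that choice of covariates is commonly left to an analysis plan that is not shown, and that section 4.4.10 is not an unadjusted analysis: its logistic step could admit previous place of delivery. That is correct, and a reader who inferred that the plan forbids or ignores all baseline adjustment would go too far. What stands is narrower. The protocol does fix a rule for covariates, and that rule makes entry depend on a p-value.

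Two further inferences fail. A reader might take the baseline as already collected for every woman. The text documents it only in the intervention procedure, through CHWs whom the control arm does not have. It does not show that control women lack the value, only that nothing secures it.

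A reader might also treat sub-study two as a ready baseline for the same outcomes. Annex 6 has no item on timely return visits or on initiation of breastfeeding. The survey samples 21 parishes that are not mapped to the 16 centres (section 4.3.6), and it takes lactating women generally, whereas the trial enrols ANC attenders up to 28 weeks.

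On size, the power gain rests wholly on an assumed correlation. Applying (1 − r²) to the whole variance would give 62%, 71% and 86%, but a centre-level term acts on the between-centre part only, so those figures are too high. It is also fair to say that the false-positive rates arise from purposive allocation, and that the missing term is a failure to limit the damage.

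**Conclusion.** The point holds in this form: the arm comparison has no fixed pre-trial term, covariates enter only through a significance screen, and the two usable baseline items are not secured in the control arm, while allocation by location makes existing differences a real threat.

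The gain in power is about 2, 8 or 18 points (from 59% to 61%, 67% or 77%) for assumed correlations of 0.3, 0.5 or 0.7, given the protocol's k, eight centres per arm and about 98 women followed per centre. It is small at the low end. The 59% itself is not caused by the missing term. The false-positive rates of 12%, 25% and 54% depend on assumed gaps of 3, 5 and 8 points.

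A reader might infer that adjustment would make the comparison unbiased. It would not: with 16 non-randomised centres and a self-reported baseline it reduces the bias and leaves some behind. The remedy reaches two of the four primary outcomes, institutional delivery and completed four visits. It is worth making because it is cheap and must be in place before enrolment.

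**What to change.** 1. **Data capture.** Move previous ANC attendance and previous place of delivery to a common enrolment record, asked in the same words in all 16 centres, or add them to the questionnaire that research assistants give in both arms.
2. **Section 4.4.10.** For institutional delivery and completed four visits, fix both items as covariates whatever their p-values, with first pregnancy as its own category. Add the centre's mean of previous facility delivery among parous women. Fit this in a model that accounts for clustering by health centre.
3. **Newborn practices.** For cord care, warmth and immunisation, show sub-study two levels by area beside the trial result, as context only. For timely return visits and initiation of breastfeeding, state that no pre-trial measure exists.
4. **Limitations (section 5.1).** Say that adjustment lessens but does not remove bias from non-random allocation.

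**Cost.** The cost is the two history items asked in both arms, some analysis wording, and linking surveyed parishes to trial areas, with no extra women or visits. One centre-level degree of freedom is spent (14 to 13). The items are self-reported, and women in a first pregnancy have no value.
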